**Fig. 2 Fig2:**
[figure not shown]
Location of the study hospitals; red ellipse represents Rajshahi Medical College Hospital, Rajshahi; red rectangle represents Jalalabad Ragib-Rabeya Medical College & Hospital; red triangle represents Khulna Medical College Hospital

Health outcomes of vaccination:

Rajshahi Medical College Hospital, Rajshahi.Khulna Medical College Hospital, Khulna.

Cost associated with influenza illness:

Rajshahi Medical College Hospital, Rajshahi.Jalalabad Ragib-Rabeya Medical College & Hospital, Sylhet.

Study sites for required capacity for a facility-based influenza vaccination objective:

We will utilize secondary data to estimate the required capacity for seasonal influenza vaccination at three hospital catchment areas, as illustrated in Table 1.

### Study population and participant recruitment

The study population will consist of persons belonging to the four high-risk groups as defined by the World Health Organization (WHO), except for healthcare workers: children six months to eight years, pregnant women, elderly ≥ 60 years, and adults with chronic diseases [7]. We have excluded healthcare workers from our targeted study population to prevent duplication with our prior research efforts [19]. We will enroll study participants who meet specific inclusion and exclusion criteria. Table 3 depicts the criteria utilized to determine the inclusion and exclusion of participants in our study.

**Table 3 Tab3:** List inclusion and exclusion criteria

Inclusion criteria	Exclusion criteria
Participants will be visiting study hospitals (outpatients and inpatients only. Not emergency departments) for routine care during the study period.	Participants with severe, life-threatening allergies to any ingredient in a flu vaccine (other than egg proteins)
Participants who will be children six months to eight years, or aged more than 60 years, or pregnant women (any trimester), or have any chronic disease such as chronic respiratory disease (requiring regular medication), diabetes, chronic renal disease, any cancer, excluding basal and squamous skin cancers, immune suppression or immune deficiency, chronic liver disease, chronic hematological disorder, chronic kidney disease, chronic neurological impairment/disease, serious mental health condition, organ or bone marrow recipient, history of any prior surgery, percutaneous coronary intervention, high blood cholesterol, family history of cardiovascular disease, other pre-existing conditions.	Participants having a history of severe allergic reactions (e.g., anaphylaxis) after a previous dose of influenza vaccine or to a vaccine component.
Participants /parents/caregivers who will be willing to sign the informed consent form	Participants having a history of Guillain-Barre syndrome less than six weeks after a previous dose of influenza vaccine.
Participants/parents/caregivers who will have an operational mobile phone number and are responsible for sharing updated phone numbers in case of plans to change for the next year	Participants having a history of moderate or severe acute illness with or without fever. The vaccine should be given after the acute condition has improved.
Participants/parents/caregivers who will have fixed addresses with no plan to leave the address for the next one year	
Participants/parents/caregivers will be aware of the follow-up schedule and understand the study expectations during the follow-up.	

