**Methods:**

We will undertake this study following STROBE guidelines. We will conduct the study in inpatient and outpatient departments of three selected tertiary-level hospitals leveraging the ongoing hospital-based influenza surveillance (HBIS) platform. The study population will include the WHO-defined four high-risk groups excluding healthcare workers: children six months to eight years, pregnant women, elderly ≥ 60 years, and adults with chronic diseases. We will collect quantitative data on participants’ acceptability, health beliefs, barriers, and vaccination intentions using the health belief model (HBM) from patients meeting the criteria for high-risk populations attending two public tertiary-level hospitals. In one of the two public tertiary-level hospitals, we will arrange an influenza vaccination campaign before the influenza season, where the vaccine will be offered free of cost to high-risk patients, and in the second hospital, vaccination will not be offered. Both the vaccinated and unvaccinated participants will then be followed-up once a month for one year to record any influenza-like illness, hospitalization, and death. Additional data for objective two will be collected from patients with symptoms of influenza-like illness (ILI) and severe acute respiratory infection (SARI) at one public and one private hospital to determine both direct and indirect costs associated with influenza illness. We will estimate the required number of influenza vaccines, safe injections, and total storage volume utilizing secondary data. We will use a deterministic Markov decision-analytic model to estimate the cost-effectiveness of facility-based influenza vaccination in Bangladesh.

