Elderly ≥ 60 years influenza vaccine doses	One dose for all persons aged 60 years and older. Population data from the Statistical Yearbook of Bangladesh 2020 [26]. Monthly the total number of ≥ 60 years aged patients visited hospitals will be collected from respected hospitals or respective District Civil Surgeon Office [29, 30, 33].
Adults with chronic diseases, influenza vaccine doses	One dose for all persons with chronic disease. We will use the prevalence of having any chronic illness from the Bangladesh Household Income and Expenditure Survey (HIES) 2010 [35]. Then, the total number of persons with any chronic illness will be estimated using data from the Statistical Yearbook of Bangladesh 2020 [26]. Monthly patients with chronic diseases visited hospitals will be collected from respected hospitals or respective District Civil Surgeon Office [29, 30, 33].

We will conduct all the study activities through close collaboration with the Institute of Epidemiology Disease Control and Research (IEDCR) of the Ministry of Health and Family Welfare (MoH&FW), the Government of Bangladesh. We will also collaborate closely with the administration of the participating hospitals, especially the hospital director, to guarantee the hospitals’ participation, support, and cooperation. We will work with the line director and directors of study hospitals to implement the vaccination. We will utilize hospital resources and leverage existing staff to vaccinate study participants. Figure 1 illustrates the study activities and data collection flow chart.

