## Study size

### Sample size and sampling

#### The sample size for the vaccine acceptability objective

Our study design will be quasi-experimental. Our primary outcome for vaccine acceptability is the intention to receive the influenza vaccine. Based on studies utilizing the high-risk group-specific health belief model conducted in neighboring countries, it has been found that 91% of elderly people, 88% of adults with chronic illness, 76.3% of pregnant women, and 62.4% of parents with six to three-year-olds expressed their intention to get the influenza vaccine [38–40, 45]. We expect a similar positive intention to receive the influenza vaccine, ranging from 62 to 91% for our target study population. In this study, we employed a significance level of 5%, a power of 80%, a design effect of 1.2, and account for a non-response rate of 10% to determine the required sample size [65–67]. We will utilize a validated health belief model tool. To avoid selection bias, we will use random assignment to the study based on predefined inclusion and exclusion criteria. We will also provide training to study staff about random enrolment of the study participants based on inclusion and exclusion criteria. Table 5 represents the estimated sample size by the high-risk group for the vaccine acceptability objective.

**Table 5 Tab5:** Estimated sample size for investigating the vaccine acceptability/ intention to receive, health outcome due to vaccination, and cost-effectiveness of implementing a facility-based influenza vaccination

High-risk group	The sample size for the vaccine acceptability survey	The sample size for vaccine effectiveness	The sample size for the cost-components survey
Children 6 months to 8 years	659	465	60
Pregnant women	495	756	39
Elderly ≥ 60 years	330	736	56
Adults with chronic diseases	425	610	31

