#### The sample size for the vaccine effectiveness objective

Our primary outcome for health outcome for vaccination is vaccine efficacy against influenza among high-risk group populations. Studies from neighboring countries found that ILI symptoms were 15.30% of children, 31.23% of adults with chronic illness, 10.97% of pregnant women, and 20% of the elderly [68–70]. A systematic review of seasonal influenza vaccine policy, use, and effectiveness also revealed that pooled vaccine effectiveness for high-risk groups in the tropics and subtropics ranged from 48 to 88% (10). We expect a similar vaccine efficacy between 50 and 81% for our study’s targeted high-risk group population. A 5% significance level, 80% power, design effect 1.2, and 10% non-response were used to calculate the required sample size to estimate vaccine effectiveness [65–67]. Table 5 represents the high-risk group’s estimated sample size for vaccine effectiveness.

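### Table 3's chronic-disease criterion admits people with no chronic disease and does not match the named group of adults with chronic diseases, nor the ≥ 60 age limit used elsewhere

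*Protocol article*

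**What the plan says.** The Abstract and the section on study population and participant recruitment list the same four groups: "children six months to eight years, pregnant women, elderly ≥ 60 years, and adults with chronic diseases". The latter section then makes the table the enrolment rule: "Table 3 depicts the criteria utilized to determine the inclusion and exclusion of participants in our study".

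In Table 3 the limb for the fourth group opens with "or have any chronic disease such as chronic respiratory disease (requiring regular medication), diabetes, chronic renal disease", continues through other diseases, and closes with "history of any prior surgery, percutaneous coronary intervention, high blood cholesterol, family history of cardiovascular disease, other pre-existing conditions". The limbs are joined by 'or', so one item is enough. No age is attached to this limb. The limb for the elderly requires an age above 60, whereas the Abstract, Table 1, the paragraph above Table 3 and Table 5 all use 60 and over.

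The planning inputs for the fourth group are described in terms of chronic illness:
- Table 1, target population: "We will use the prevalence of having any chronic illness from the Bangladesh Household Income and Expenditure Survey (HIES) 2010".
- Vaccine acceptability sample size: "91% of elderly people, 88% of adults with chronic illness, 76.3% of pregnant women".
- Vaccine effectiveness sample size: "ILI symptoms were 15.30% of children, 31.23% of adults with chronic illness, 10.97% of pregnant women, and 20% of the elderly".
- Cost-components sample size: a direct cost of USD 75 for adults with chronic diseases.

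Under vaccine efficacy estimation, effectiveness with a 95% CI is to be reported for each risk group.

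**The concern.** Prior surgery is a past event, and a family history is someone else's illness. Neither requires the participant to have a chronic disease, yet either one qualifies a patient for the chronic-disease group. The closing item can take in almost anything a recruiter chooses to count.

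The results are produced and used by group. If part of this group has no chronic disease, its intention to be vaccinated, its vaccine effectiveness and its illness cost are averages over a mixture. Those averages would be attached to a population counted by prevalence of chronic illness and reported as evidence on adults with chronic disease. The cost survey plans only 31 people in this group, so a few who do not belong could move its mean.

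**Working it through.** **Side-by-side reading.** The claim concerns wording and rests on no figure in the plan.

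| Point | Named population and other sections | Table 3 |
|---|---|---|
| Fourth group | Has a chronic disease | A chronic disease, or any past operation, or a family history of cardiovascular disease, or an undefined other condition |
| Age, fourth group | Adults | Not stated |
| Elderly | 60 and over | Above 60 |

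Consequences of the table as written:
1. An outpatient whose only qualifying feature is a past operation or an affected relative is eligible as chronic-disease.
2. A person aged 9 to 17 with a listed item meets the table but fits no row of Table 5.
3. If 'more than 60' is read in completed years, a person aged exactly 60 with no other qualifying feature is in the named group but fails the table.

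Nothing in the article narrows the two non-disease items. Percutaneous coronary intervention and high cholesterol, in the same string, do point to chronic conditions, and the finding does not rely on them.

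**Could the mixture matter to the effectiveness sample size?** This is an illustration only; the share *s* and the risk *r* are assumptions.

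Inputs from the plan: ILI risk 31.23%; the low end of expected efficacy, 50%; 5% significance (taken as two-sided); 80% power; design effect 1.2; 10% non-response; sample size 610 (taken as the total, since the article does not say whether it is per arm).

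Formulas:
- group risk = (1 − s) × 31.23% + s × r
- two-proportion sample size with pooled variance; total = 2 × n per arm × 1.2 / 0.9

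Results:
- *s* = 0: 115 per arm; 2 × 115 × 1.2 / 0.9 = 307 in total.
- *s* = 10%, *r* = 20%: risk 0.9 × 31.23 + 0.1 × 20 = 30.1%; 120 per arm; total 320.
- *s* = 50%, *r* = 10%: risk 0.5 × 31.23 + 0.5 × 10 = 20.6%; 192 per arm; total 512.

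With 610 in total, the effective number per arm is 610 × 0.9 / 1.2 / 2 = 229. Power at 50% efficacy is then 98% with no dilution and 86% at *s* = 50%, *r* = 10%. It falls below 80% only in more extreme cases; for example, *s* = 75% with *r* = 10.97% gives a risk of 16.0% and power of about 75%. At higher efficacy the power is greater. The figure of 610 is not itself reproduced by these inputs; that is a separate matter.

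**The case against.** **Most of the list is sound.** The governing words are 'any chronic disease', most listed items are genuine chronic diseases, and the last item can be read as other chronic conditions. This stands: the cohort is broader at its edge, not a different group. It does not rescue prior surgery and family history, which the table names outright.

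**The missing adult age is mostly covered.** The paragraph directly above Table 3 says adults, so a 12-year-old with asthma is outside the stated population. What remains is a gap between table and text.

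**Recruitment is from tertiary hospitals.** Patients attending for routine care are less likely to be free of chronic disease than the public. This may limit the share affected but does not remove it.

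**Stronger readings that the document does not support:**
- *Cases averted fall by 9% to 49%, and the cost-effectiveness ratio moves with them.* Those figures follow if 25–75% of the group have no chronic disease and carry an ILI risk of 20% or 10.97%: 1 − 28.42/31.23 = 9% and 1 − 16.04/31.23 = 49%. The shares have no source, and the risks belong to the elderly and pregnant women. The section on data sources for disease burden takes outpatient visits, hospitalisations and deaths from secondary sources, so a lower risk among enrollees need not reach the model.
- *The cohort contradicts the objectives.* The Objectives speak only of high-risk groups; the specific label comes from the Abstract and the population section.
- *The vaccinated and control hospitals will apply the catch-all differently and bias effectiveness.* This is possible with one hospital per arm, but nothing in the document shows it.
- *Every planning input rests on the same strict definition of chronic illness.* The article labels them so, but the cited sources' definitions are not shown.

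**Conclusion.** The point holds as a stated eligibility rule that is wrong for the group it serves. Table 3 allows entry to the chronic-disease group without a chronic disease, through two named items and an unbounded one. It also differs from the rest of the article on the elderly age limit and leaves out the word adults.

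What is affected is the meaning of the group's intention, effectiveness and cost estimates, and their match to the chronic-illness population to which they are applied. The size is unknown, because the share entering only through the non-disease items is not given. Under the assumptions above, power at 50% efficacy stays at 86% or more for shares up to one half if 610 is the total. Neither a loss of power nor a change in the cost-effectiveness ratio is shown. The correction is worth making because it is cheap and the results are meant to inform policy for this group.

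**What to change.** Reconcile Table 3 with the population paragraph:
1. Remove prior surgery and family history of cardiovascular disease as conditions that qualify on their own.
2. Reword the final item as other chronic disease. Do not restrict the group to the diseases listed: genuine chronic conditions that the table does not name enter only through 'such as' or the catch-all, and a closed list would lose them.
3. State adults for this limb, and use ≥ 60 for the elderly.

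Enrolment began in March 2022, so the amendment alone is not enough. For those already enrolled, use the medical history described under quantitative variables, where it captures the qualifying condition. Define the chronic-disease analysis group as adults with at least one chronic disease, listed or not, and report separately those who entered only through the non-disease items.

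The cost is an amendment to one table and a classification step, with a somewhat smaller analysed chronic-disease group. The article mentions medical history only in general terms, so whether it records the qualifying condition should be checked first.

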### Variables

We thoroughly reviewed the literature on different outcome variables and explanatory factors in our research [5, 31, 36–44]. Regarding our first objective, which centered on vaccine acceptability, our primary outcome of interest wil be the high-risk groups’ intention to receive the influenza vaccination. This will assist us in assessing the propensity of high-risk groups’ willingness to receive influenza vaccine. Our second objective focuses on vaccination effectiveness, precisely measuring vaccine efficacy against influenza in high-risk group groups. This metric will enable us to assess the efficacy of the vaccination in protecting high-risk group groups. In addition, we will thoroughly examine the cost components related to influenza, focusing on the overall costs of influenza-related illnesses in high-risk groups as our second objective’s variables. To understand the complex factors that affect vaccine acceptance and effectiveness, we will examine various explanatory variables, including age, gender, occupation, location, marital status, and income, among others.

### Data sources and measurement

#### Data collection to assess health beliefs, barriers, and intention to receive an influenza vaccine

We will collect data on acceptability, health beliefs, obstacles, and current intentions to receive the vaccine from enrolled participants (Fig. 2). We will capture these data using the health belief model (HBM). The questionnaire has been developed using an existing literature review [36–41, 45]. We will include items to assess five theoretical constructs of HBM based on reviewing relevant literature, including high-risk individual’s perceived susceptibility to disease, perceived severity of influenza, perceived benefits of the vaccine, perceived barriers to the vaccine, cues to action, and self-efficacy [37, 38, 46]. We will conduct face-to-face interviews for the data collection.

### Data collection to determine vaccination cost-effectiveness

#### Vaccination campaign

To record health outcomes after influenza vaccination, in one of the two public tertiary-level study hospitals, we will conduct an influenza vaccination campaign before the influenza season, where the vaccine will be offered free of cost to high-risk patients, and in the second hospital, vaccination will not be offered. We will work with the hospital administration to set up a vaccination booth on the hospital premises. Vaccines will be made available at the vaccination booths. Posters and leaflets containing information on influenza vaccination will be displayed at the vaccination booths and key hospital locations with information on the vaccination. Inpatients and outpatients of all departments will be informed about the ongoing immunization campaign. Eligible patients will be offered to take the vaccine during the vaccination campaign. Benefits, significance, adverse effects, and how to manage them will be explained to the patients. Nurses/ Health Assistants (HA) will provide influenza vaccination throughout the campaigns. At 8 AM, the vaccination booth will open and close at 2 PM, six days a week throughout the campaign period. A vaccination card will be issued to the participants. All high-risk groups will get one dose of seasonal influenza vaccination (Quadrivalent), except children aged six months to 8 years, who will receive two doses four weeks apart [31, 32]. All vaccines will be the southern hemisphere vaccine as recommended by the WHO for Bangladesh. Regarding children, we will make phone follow-ups with the guardians of the children receiving the first dose to remind them about the second dose schedule, and it will be recorded in the vaccine card if the second dose is received. In order to ensure the availability and quality control of vaccines throughout the three-month campaign period, the research team at icddr,b will closely monitor the campaign. All vaccinated participants will receive notification regarding potential adverse events following immunization (AEFI) during the vaccination process. To document any untoward occurrences after Adverse Events Following Immunization (AEFI), we will adhere to the pre-existing surveillance mechanism implemented by the World Health Organization (WHO) and the Ministry of Health and Family Welfare (MoHFW) of the government of Bangladesh. During the vaccination campaign briefing session in each study hospital, participants will be informed about the process of reporting any Adverse Events Following Immunization (AEFI) within the hospital’s established surveillance system. Additionally, participants will be provided with the mobile number, as stated in the consent form, to report any such issues. Furthermore, during the vaccination campaign implementation, a representative from icddr,b will be assigned to each study hospital to oversee and monitor any adverse events following immunization (AEFI) in conjunction with the hospital’s existing surveillance system. If an Adverse Event Following Immunization (AEFI) case is identified, the personnel affiliated with icddr,b will promptly notify the Hospital Surveillance Officer (HSO), provide support to the HSO in completing the AEFI report form, and subsequently transmit it to the Expanded Programme on Immunization (EPI) headquarters via the Chief Health Officer.

In the second hospital, we will enroll participants meeting the high-risk group individual criteria. However, no vaccination campaign will be conducted. We will name this group as an unvaccinated cohort.

